# SAMPLE SIZE AND STATISTIC EVALUATION

As this is a descriptive study, there will be no hypothesis testing. The sample size is calculated based upon a desired margin of error for the proportion of subjects reaching the target HbA1c level.

In the 2007 Chinese Guideline for Diabetes Prevention and Treatment [20], the target HbA1c level was set to be <6.5%,. However, in the newest Chinese Guideline published in November 2011 [19], the target HbA1C level has been adjusted to <7.0%, based on the evidence showing that HbA1c<7.0% is already associated with decreased incidence of diabetic complications and that further reduction of HbA1c with using more aggressive intervention might result in an increased incidence of hypoglycemia. In patients with cardiovascular complications, further reduction of HbA1C beyond 7.0% may even be associated with increased risk of CV events. On the other hand, for newly diagnosed patients, the latest guideline still recommended to aim for normal level of HbA1C (<6.5%) by using insulin or other ADT (anti-diabetic treatment) with low risk of hypoglycemia. The target HbA1C level for this study is thus set to be consistent with the guideline, i.e. 6.5%.

According to the results of the Polish ARETAEUS1 study [19], 28.9% of the patients who were diagnosed with T2D within 2 years achieved a therapeutic target of HbA1C <6.5%. Pan et al [14] reported 25.9% of T2D patients in China achieved a target glycemic control level of HbA1C <6.5%. A recently completed CCMR study showed that 30.7% of the stabilized T2D patients (diagnosed more than 6 months) in China reached this therapeutic target. We thus estimate that the proportion of newly T2D patients reaching the target of HbA1c < 6.5% in this study is approximately between 26%-31%.

Assuming a confidence level of 95%, a confidence interval of 0.05 (margin of error of +/- 2.5%), and the expected proportion (p) of 0.30, n=1,315 subjects are required. To ensure each of the three hospital tier has sufficient subjects to demonstrate the assumed proportion of patients reaching the target HbA1c <6.5%, the total sample size would be n=3,945 (1,315 x 3). Attrition is often a challenge in observational studies and three recent, large population-based observational studies of diabetes patients in China reported attrition rates ranging from 14% to 25%. Assuming an attrition rate of approximately 20% for this study, a sample size of 4,931 is required.

Demographics and baseline characteristics will be summarized. Multivariate regression analysis will be performed to identify independent predictor of treatment outcomes. Specific subgroups will be compared with respect to their baseline characteristics, diabetes history, cardiovascular risk factors, clinical outcomes, microvascular and macrovascular events. Cox hazard regression model or logistic regression model will be used to assess relative risks of baseline characteristics, cardiovascular risk factors, and other independent factors by using incidence of inadequate glycemic control as dependent variables. An interim analysis of baseline data will be performed upon completion of patient enrollment, in addition to the final study analysis.

For diabetes knowledge assessment and EQ-5D questionnaire, the results will be analyzed using descriptive statistics; comparative analysis will be conducted between the baseline EQ-5D and the last visit results.

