| Sample Size and Statistic Evaluation | As this is a descriptive study, there will be no hypothesis testing. The sample size will be calculated based upon a desired margin of error for the proportion of subjects reaching the target HbA1c level.  According to the results of the Polish ARETAEUS1 study, 28.9% of the patients who were diagnosed with T2D within 2 years achieved a therapeutic target of HbA1c <6.5%. Pan et al reported 25.9% of T2D patients in China achieved a target glycemic control level of HbA1c <6.5%. A recently completed CCMR study showed that 30.7% of the stabilized T2D patients (diagnosed more than 6 months) in China reached this therapeutic target. We thus estimate that the proportion of newly T2D patients reaching the target of HbA1c < 6.5% in this study is approximately between 26%-31%.  Assuming a confidence level of 95%, a confidence interval of 0.05 (margin of error of +/- 2.5%), and the expected proportion (p) of 0.30, n=1,315 subjects are required. To ensure each of the three hospital tier has sufficient subjects to demonstrate the assumed proportion of patients reaching the target HbA1c <6.5%, the total sample size would be n=3,945 (1,315 x 3). Attrition is often a challenge in observational studies and three recent, large population-based observational studies of diabetes patients in China reported attrition rates ranging from 14% to 25%. Assuming an attrition rate of approximately 20% for this study, a sample size of 4,931 is required.  Demographics and baseline characteristics will be summarized. Multivariate regression analysis will be performed to identify independent predictor of treatment outcomes. Specific subgroups will be compared with respect to their baseline characteristics, diabetes history, cardiovascular risk factors for glycemic control, clinical outcomes, and vascular events. Cox hazard regression model or logistic regression model will be used to assess relative risks of baseline characteristics or other factors, by using incidence of inadequate glycemic control as dependent variables and baseline risk factors as independent variables.  An interim analysis of the baseline data will be performed upon completion of patient enrollment, in addition to the final study analysis.  For diabetes knowledge assessment and EQ-5D questionnaire, the results will be analyzed using descriptive statistics; comparative analysis will be conducted between the baseline EQ-5D and the last visit results. |

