# OBSERVING ENDPOINTS

## Primary endpoints

The overall proportion of patients whose HbA1c is less than 7%, measured at the end of one year follow up.

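### The primary endpoint is HbA1c <7%, but the study target and the sample size are set at HbA1c <6.5%, so the primary endpoint has no planning proportion or stated precision

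*Protocol*

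**What the plan says.** **Endpoint.** Section 6.1 gives the primary endpoint as "The overall proportion of patients whose HbA1c is less than 7%, measured at the end of one year follow up". The synopsis row on observational endpoints uses the same words. No primary or secondary endpoint names 6.5%.

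**Study target.** Section 7 reports that the newest national guideline moved the general target to below 7.0%, notes a stricter aim for newly diagnosed patients, and concludes: "The target HbA1C level for this study is thus set to be consistent with the guideline, i.e. 6.5" (per cent).

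**Sample-size basis.** Section 7 states: "The sample size is calculated based upon a desired margin of error for the proportion of subjects reaching the target HbA1c level". Its three source rates (28.9%, 25.9%, 30.7%) are all for HbA1c below 6.5%, and so is the planning range: "We thus estimate that the proportion of newly T2D patients reaching the target of HbA1c < 6.5% in this study is approximately between 26%-31" (per cent). The calculation follows: "a confidence interval of 0.05 (margin of error of +/- 2.5%), and the expected proportion (p) of 0.30, n=1,315 subjects are required". It is then multiplied across tiers for "the assumed proportion of patients reaching the target HbA1c <6.5%, the total sample size would be n=3,945 (1,315 x 3"), and inflated: "Assuming an attrition rate of approximately 20% for this study, a sample size of 4,931 is required". The synopsis sample-size row repeats the 6.5% basis.

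**Dependent terms.** Secondary endpoint 3 counts patients who reach the therapeutic target at 3, 6, 9 and 12 months. The Cox or logistic regression in Section 7 uses inadequate glycemic control as its outcome. Neither carries a number. The Background attaches the term therapeutic target to below 7.0%, while Section 7 attaches it to below 6.5%.

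**The concern.** The study tests no hypothesis, so its main product is one proportion with a stated precision. Here the proportion and the precision belong to different definitions. The +/-2.5 points and p = 0.30 describe patients below 6.5%; the declared result is for patients below 7%.

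The protocol also makes a study-level statement about its target that disagrees with its primary endpoint. The two definitions differ by the share of patients with HbA1c from 6.5% to just under 7.0%. The document does not give that share, but once it exceeds 2.5% of patients, the choice of cut-off moves the estimate by more than the stated margin.

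The disagreement carries over to secondary endpoint 3 and to the regression outcome, whose terms the protocol supports at either cut-off. A later analysis plan could not settle this without overriding one of the protocol's statements.

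**Working it through.** **Inputs from Section 7:** 95% confidence (z = 1.96), half-width e = 0.025, p = 0.30 for HbA1c <6.5%, three tiers, 20% attrition. The document gives no proportion for HbA1c <7%, so a range is shown below as an assumption.

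**Step 1: reproduce the plan's figure.** n = z²p(1-p)/e².
- p = 0.30: 3.8416 × 0.21 / 0.000625 = 1,290.8, so 1,291. This is 1.8% below the stated 1,315.
- p = 0.31, the top of the stated range: 3.8416 × 0.2139 / 0.000625 = 1,314.8, so 1,315 exactly.
- 1,315 × 3 = 3,945, and 3,945 / 0.8 = 4,931.25, stated as 4,931.

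The arithmetic is sound for <6.5%. The fault is the endpoint it was applied to, not the calculation.

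**Step 2: what is known about the proportion below 7%.** Everyone below 6.5% is also below 7%, so the second proportion cannot be lower than the first. Nothing more follows from the document.

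**Step 3: precision for <7% with the planned numbers.** Half-width = 1.96 × √(p(1-p)/n).

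| Assumed proportion <7% | Per tier, n = 1,315 | Overall, n = 3,945 |
| --- | --- | --- |
| 0.30 | 2.48 points | 1.43 points |
| 0.40 or 0.60 | 2.65 | 1.53 |
| 0.50 (worst case) | 2.70 | 1.56 |
| 0.75 | 2.34 | 1.35 |

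**Step 4: when the per-tier margin exceeds 2.5 points.** With n = 1,315 this requires p(1-p) > 0.025² × 1,315 / 1.96² = 0.2139, that is, p between about 0.31 and 0.69. Outside that range the per-tier margin is no wider than stated.

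The overall column assumes 1,315 evaluable patients in each tier. Both columns treat patients as independent, with no allowance for clustering within hospitals.

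**The case against.** The strongest reply is that the primary endpoint is not ambiguous. It appears in identical words in both places where endpoints are defined, with a cut-off and a time point, and the 6.5% sentence sits in the sample-size rationale. This stands: an analyst has a clear definition to follow. A reader might infer that two analysts would report different primary proportions, but the document does not support that. The ambiguity lies in the declared study target, secondary endpoint 3 and the regression outcome.

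A reader might also infer that the study is too small. Holding +/-2.5 points per tier at p = 0.50 would take 1,537 per tier, or 1,537 × 3 / 0.8 = 5,764 enrolled, against 4,931. This does not follow either. The proportion below 7% need not lie near 0.5; at 0.75 only 1,153 per tier would be needed. The primary endpoint is the overall proportion, whose margin stays well inside 2.5 points at any value. The protocol also states: "As this is a descriptive study, there will be no hypothesis testing". No power is at stake.

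Third, a reader might express the gap between the two definitions as a multiple of the stated margin. That needs the share of patients between the cut-offs, for which the document gives no figure.

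Two further points are fair. The cut-off for a regression outcome is commonly left to the analysis plan, so its absence alone is no fault; here it matters because the protocol points to two different targets. And stating a per-tier margin for an overall endpoint is a separate mismatch, which would remain if every section used 7%.

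**Conclusion.** The contradiction holds and is in current text, in both the synopsis and the body. The primary endpoint is HbA1c <7%; the declared study target and the whole sample-size basis are <6.5%. The sized proportion is not an endpoint, and the endpoint has no planning proportion or precision of its own.

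The numerical cost is small: at worst 0.20 points per tier (2.70 against 2.50), with the overall margin at most 1.56 points. These are upper bounds over every possible proportion, so they do not depend on an assumed rate below 7%. They do rest on 1,315 evaluable patients per tier and on simple random sampling. The point should be corrected because of what the result means, not because of the sample size.

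**What to change.** Reconcile the synopsis, Section 6.1 and Section 7 so that the primary endpoint, the study target and the sample-size basis use the same threshold. State which threshold secondary endpoint 3 and the regression outcome use. If the other threshold is kept, name it as a separate secondary endpoint. Which threshold is clinically right is for the sponsor and investigators, not this review.

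If <7% stays primary, restate the precision without relying on a <6.5% rate: at most about +/-2.7 points per tier and +/-1.6 points overall, before any design effect. Giving both levels also aligns the margin with the overall endpoint.

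The cost is protocol wording and a slightly less favourable per-tier figure. No added patients, visits or procedures are needed.

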**[name] on behalf of CCMR Executive Committee**

Chairman of CCMR Executive Committee

Chief Scientific Officer

VitalStrategic Research Institute

SYNOPSIS

| Study Type | Observational, longitudinal, prospective cohort study |
| --- | --- |
| Study Subjects | Newly diagnosed type 2 diabetic (T2D) patients defined as diagnosis of T2D according to the Chinese Guideline (2010) for Type 2 Diabetes, within the past 6 months. |
| Number of Subjects | Approximately 5000 patients from nation-wide hospitals will be recruited |
| Study Location | Approximately 80 hospitals (40 tier 3, 25 tier 2, 15 tier 1) from 6 major geographic regions in China will be recruited for this study. |
| Principal Investigator | [name], Director of Endocrinology Department, Beijing University, People’s Hospital, Beijing, China |
| Investigators | Qualified internists and endocrinologists will be selected from the members of CEA and other CCMR physician networks. |

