# STUDY DESIGN

## General design

Any newly diagnosed (within 6 months) type 2 diabetic patient who is visiting tier 3, 2, or 1 hospitals, may be considered for enrollment in this study, as long as the patient meets the inclusion and exclusion criteria and is willing to sign on the informed consent form.

Enrolled patients will receive routine treatment (diet & exercise or medication) and will be asked to return to the same investigator for follow up visits at 3, 6, 9 and 12 month after the baseline visit.

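### The ±2.5% margin per hospital tier makes no allowance for clustering within about 80 hospitals and is missed at almost any positive intracluster correlation

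*Protocol*

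**What the plan says.** Section 7 of the protocol describes a descriptive study without hypothesis tests, so the width of a confidence interval is the only basis for its size. The inputs are "Assuming a confidence level of 95%, a confidence interval of 0.05 (margin of error of +/- 2.5" percentage points) and "the expected proportion (p) of 0.30, n=1,315 subjects are required". The number is then tripled: "To ensure each of the three hospital tier has sufficient subjects to demonstrate the assumed proportion of patients" reaching the HbA1c target, "the total sample size would be n=3,945 (1,315 x 3"). Finally, "Assuming an attrition rate of approximately 20% for this study, a sample size of 4,931 is required". The ±2.5% is therefore a promise made for each tier.

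The Synopsis (Study Location) plans "Approximately 80 hospitals (40 tier 3, 25 tier 2, 15 tier 1) from 6 major geographic regions in China". Under Section 4.1, patients "will be asked to return to the same investigator for follow up visits at 3, 6, 9 and 12 month", and Section 4.3 excludes those who cannot keep returning to the same hospital. The primary endpoint in Section 6.1 is the overall proportion, not a proportion per tier. Section 7 mentions no intracluster correlation or design effect. It names logistic or Cox regression without reference to hospital and does not say how the interval for the primary proportion will be computed.

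**The concern.** Patients treated at one hospital, by the same investigator throughout, share prescribing habits, case mix and local resources. Their chances of reaching the HbA1c target are likely to be positively correlated. A sample of hospitals then carries less information than the same number of independent patients, and the loss grows with the number of patients per hospital. Tier 1 is most exposed because it has only 15 hospitals.

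The protocol gives its own reason to expect such differences. Sections 3.2 and 6.2 list physician specialty and years of practice among the factors to be studied, and these can vary between hospitals of the same tier. At stake is the one statistical claim the sample size makes, that each tier's proportion will be known to within 2.5 points.

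**Working it through.** **Inputs from the protocol.** Section 7: 95% confidence, half-width d = 0.025, p = 0.30 (the plan says the proportion "is approximately between 26%-31"%), 1,315 per tier, 3,945 in total, 20% attrition. Synopsis: 40, 25 and 15 hospitals in tiers 3, 2 and 1.

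**Assumptions.** The ICC is not in the documents; 0.01, 0.02 and 0.05 are used. Hospitals are taken as equal in size within a tier.

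**Reproducing the plan's figure.** n = 1.96² × p(1−p)/d².
- At p = 0.30: 1,290.7, so 1,291.
- At p = 0.31, the top of the stated range: 1,314.7, so 1,315.
- 3 × 1,315 = 3,945, and 3,945/0.80 = 4,931.25 (stated as 4,931).

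The plan's 1,315 exceeds 1,291 by 1.9%. No design effect is hidden in it.

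**Per-tier margins.** Completers per hospital are m = 1,315/40 = 32.9, 1,315/25 = 52.6 and 1,315/15 = 87.7. The design effect is DE = 1 + (m−1) × ICC, and the margin is 1.96 × √(0.21 × DE/1,315). Without clustering the margin is ±2.48%.

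| ICC | Tier 3: DE, margin | Tier 2: DE, margin | Tier 1: DE, margin |
|---|---|---|---|
| 0.01 | 1.32, ±2.84% | 1.52, ±3.05% | 1.87, ±3.38% |
| 0.02 | 1.64, ±3.17% | 2.03, ±3.53% | 2.73, ±4.09% |
| 0.05 | 2.59, ±3.99% | 3.58, ±4.69% | 5.33, ±5.72% |

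**Break-even per tier.** The margin reaches ±2.5% at DE = 1,315/1,290.7 = 1.0188. The corresponding ICC is 0.0188/(m−1), about 0.0006 in tier 3, 0.0004 in tier 2 and 0.0002 in tier 1.

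**Overall proportion.** With 3,945 completers spread equally over 80 hospitals, m = 49.3. Without clustering the margin is ±1.43%.

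| ICC | DE | Margin | Coverage of a nominal 95% interval that ignores hospital |
|---|---|---|---|
| 0.01 | 1.48 | ±1.74% | 89% |
| 0.02 | 1.97 | ±2.01% | 84% |
| 0.05 | 3.42 | ±2.64% | 71% |

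Coverage is 2Φ(1.96/√DE) − 1. The overall margin reaches ±2.5% at DE = 3,945/1,290.7 = 3.06, that is at ICC = 2.06/48.3, about 0.043.

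**Sensitivity of the overall result.** The tier table assumes 1,315 per tier and the overall table assumes equal hospitals; both cannot hold at once. Under 1,315 per tier with equal tier weights, the average of the three design effects is 1 + 56.7 × ICC, where 56.7 = (31.9 + 51.6 + 86.7)/3. The overall margins become ±1.79%, ±2.09% and ±2.80%, and the break-even ICC is 2.06/56.7, about 0.036. The conclusion is the same.

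**Would more patients help?** With the hospitals fixed at k, an effective sample of 1,315 needs n = 1,315(1−ICC)/(1 − 1,315 × ICC/k). At ICC 0.01 this is 1,940, 2,747 and 10,556 completers in tiers 3, 2 and 1. At ICC 0.02 the denominator is negative in tiers 2 and 1, so no number of patients in those hospitals is enough.

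**The case against.** The strongest reply is that the primary endpoint is the overall proportion and that tripling the sample leaves it a reserve. This stands. A reader might infer that the study cannot deliver ±2.5% on its primary endpoint. The figures do not support that below an ICC of about 0.043 (0.036 with equal tier sizes), which covers most of the assumed range.

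A reader might also infer that the reported intervals will be too narrow and that regression predictors will look too certain. That follows only if the analysis ignores hospital. Section 7 names the models in outline, fixes no interval or variance method, and a statistical analysis plan that is not shown may use clustered variance. The coverage figures are therefore conditional. They also belong to the overall estimate and not to the tiers.

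The evidence for correlation has limits. Differences between tiers create no correlation within a tier. Section 5.2 requires one laboratory method (HPLC) for HbA1c and Section 9.2 requires laboratory certification at each site, which limits the part that comes from measurement. Differences in practice and case mix between hospitals remain. No ICC is documented, so the size of the shortfall is uncertain, but the per-tier break-even is so low that this hardly matters.

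Finally, the study is descriptive and no decision depends on ±2.5%. That lowers the consequence, but it does not make the stated margin correct. An analysis plan could widen the intervals; it could not make 1,315 clustered patients per tier deliver the margin stated in the protocol.

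**Conclusion.** The point holds for the per-tier precision. Section 7 derives 1,315 from a formula for independent patients and promises ±2.5% in each tier, while its design clusters them in 40, 25 and 15 hospitals. Because the unclustered margin is already ±2.48%, almost any positive ICC breaks the promise. Over the assumed range of 0.01 to 0.05 the tier margins run from ±2.8% to ±5.7%, worst in tier 1.

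For the overall primary proportion the loss is a wider interval, ±1.7% to ±2.6% in place of ±1.43%, and in most of the range still within ±2.5%. Under-coverage is a risk only if hospital is ignored in the analysis, which the protocol does not settle.

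These figures rest on the assumed ICC range, equal-sized hospitals within a tier and the plan's p = 0.30. Unequal hospital sizes would generally widen the margins further.

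**What to change.** In Section 7:
- State an assumed ICC range, with its justification, and the design effect 1 + (m−1) × ICC.
- Replace the single ±2.5% with the achievable margins per tier and overall across that range.
- State that the intervals for the overall and tier proportions will use hospital-clustered variance with a small-cluster correction, which matters most for the 15 tier 1 hospitals.

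Enrolment need not rise: with the number of hospitals fixed, extra patients cannot reasonably restore ±2.5% in tier 1.

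The cost is a less favourable stated precision and slightly more analysis work. Patients are already enrolled and followed by hospital, so no new visits or data are needed.

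### The sample size assumes three equal hospital tiers, but the recruitment plan does not secure that split, so the ±2.5% margin is not assured in tier 1

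*Protocol*

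**What the plan says.** Section 7 of the protocol (Sample Size and Statistic Evaluation) sizes the study on the precision of one proportion: "Assuming a confidence level of 95%, a confidence interval of 0.05 (margin of error of +/- 2.5%), and the expected proportion (p) of 0.30", from which "n=1,315 subjects are required". It then scales up by tier. The purpose is given as "To ensure each of the three hospital tier has sufficient subjects to demonstrate the assumed proportion", and the result is "the total sample size would be n=3,945 (1,315 x 3"). The last step is "Assuming an attrition rate of approximately 20% for this study, a sample size of 4,931 is required".

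The Study Location row of the synopsis plans "Approximately 80 hospitals (40 tier 3, 25 tier 2, 15 tier 1"). The synopsis gives the number of subjects as a single figure of about 5,000, without a split by tier or by hospital. Section 4.1 (General design) lets any eligible newly diagnosed patient at a tier 3, 2 or 1 hospital be considered. Section 9.3 allows an estimated 6 months for enrolment. The primary endpoint in section 6.1 is an overall proportion, not a tier-specific one.

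**The concern.** The factor of three is the only reason the study needs about 4,931 patients rather than about 1,644. It delivers what it promises only if the tiers are filled equally. The hospitals are divided 50% / 31% / 19%, and the protocol shows no enrolment target, cap or per-hospital number that would turn this unequal mix into equal tiers.

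At stake is the accuracy of the precision statement for each tier, above all tier 1. Tier matters to the study: hospital tier is listed among the influential factors in secondary objective 2, and type of hospital in secondary endpoint 4. The number of patients each tier enrols is settled during recruitment, so an analysis plan cannot restore it afterwards.

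**Working it through.** **Inputs from the protocol.** 95% confidence, half-width m = 0.025, p = 0.30, 1,315 per tier and attrition of 20% (section 7). Section 7 also cites studies that "reported attrition rates ranging from 14% to 25" per cent, and expects that the proportion "in this study is approximately between 26%-31" per cent. Hospitals 40 / 25 / 15 and about 5,000 patients (synopsis). The protocol's p refers to HbA1c below 6.5%, and I use it as given.

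**Reproducing the plan's figure.** n = 1.96² × p(1 − p) / m².
- p = 0.30: 3.8416 × 0.21 / 0.000625 = 1,291, which is 1.8% below 1,315.
- p = 0.31, the top of the stated range: 1,315.
- 1,315 × 3 = 3,945, and 3,945 / 0.80 = 4,931.

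The stated figures stand.

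**What the equal split requires.** Enrolled per tier: 1,315 / 0.80 = 1,644. Per hospital: 1,644 / 40 = 41 in tier 3, 1,644 / 25 = 66 in tier 2 and 1,644 / 15 = 110 in tier 1. The planned average is 4,931 / 80 = 61.6, or 5,000 / 80 = 62.5. A tier 1 hospital would have to enrol about 2.7 times as many patients as a tier 3 hospital.

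**What the hospital mix yields if every hospital enrols equally** (my assumption; the protocol gives no rate). Evaluable n = N × (tier hospitals / 80) × (1 − attrition); half-width = 1.96 × √(0.21 / n).

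| Tier | Evaluable at 20% attrition, N = 4,931 / 5,000 | Half-width | Evaluable over 14% to 25% attrition, both N | Half-width |
| --- | --- | --- | --- | --- |
| 3 | 1,972 / 2,000 | ±2.02% / 2.01% | 1,849 to 2,150 | ±2.09% to 1.94% |
| 2 | 1,233 / 1,250 | ±2.56% / 2.54% | 1,156 to 1,344 | ±2.64% to 2.45% |
| 1 | 740 / 750 | ±3.30% / 3.28% | 693 to 806 | ±3.41% to 3.16% |

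Tier 1 reaches 56% to 57% of 1,315 at 20% attrition and misses ±2.5% throughout the quoted attrition range. Tier 2 meets 1,315 at 14% attrition and falls 5% to 6% below it at 20%. With equal enrolment per hospital, giving tier 1 its 1,315 would take 1,643.75 × 80 / 15 = about 8,767 patients in total.

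**Sensitivity to the unstated rate** (N = 4,931, 20% attrition, so 3,945 evaluable). If tier 1 hospitals recruit at r times the rate of the others, tier 1's share is 15r / (65 + 15r).
- r = 0.5: 7.5 / 72.5 × 3,945 = about 408, or ±4.4%.
- r = 2: 30 / 95 × 3,945 = about 1,246, or ±2.5%.
- Tier 1 reaches one third at r = 65 / 30 = about 2.2. Tier 2 then falls to about 1,012, or ±2.8%.

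**The overall proportion.** With 3,945 evaluable: 1.96 × √(0.21 / 3,945) = ±1.4%.

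All these half-widths treat patients as a simple random sample. Clustering within hospitals would widen them, with most uncertainty in tier 1, which has 15 sites.

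**The case against.** Unequal hospital numbers do not in themselves contradict equal tiers, because hospitals may enrol different numbers. The protocol gives no enrolment rate per hospital, and its count of 80 hospitals is approximate. A reader might infer that the plan will certainly leave tier 1 far short. The documents do not support that: at twice the rate of other hospitals, tier 1 comes close to its requirement. It is also fair to say that 1,315 evaluable per tier is already a target of a kind. What is absent is a recruitment control that enforces it.

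The loss of precision is moderate and falls mainly on one tier. The study is descriptive with no hypothesis testing, its primary endpoint is the overall proportion, and no listed endpoint is HbA1c control by tier. All of this stands and limits the point to a precision statement.

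A reader might go further and infer that the recruitment mix distorts the pooled primary proportion. The documents do not establish this. They give no tier-specific proportions from which to size a shift, and no distribution of patients by tier that would make equal weights more correct than the mix recruited. How the overall figure is weighted is also commonly left to an analysis plan.

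What the objection does not remove is that the sole stated reason for tripling the sample depends on an equal split that the recruitment plan does not secure.

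**Conclusion.** The point holds as a mismatch within the protocol. The sizing relies on about 1,644 enrolled patients in each tier, and the recruitment plan as written neither requires this nor makes it likely at equal enrolment per hospital. On that assumption with 20% attrition, tier 1's margin is about ±3.3% instead of ±2.5%. The size of the shortfall depends on the unknown tier 1 recruitment rate: from about ±4.4% at half the rate of other hospitals to about ±2.5% at twice the rate. Tier 2 is essentially on target under equal enrolment and tier 3 is better than planned. The claim that needs correcting is that every tier has enough patients for ±2.5%.

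**What to change.** Choose one of two routes.

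1. **Restate the precision.** Give the margin expected in each tier under the planned hospital mix: about ±2.0% in tier 3, ±2.5% to 2.6% in tier 2 and ±3.3% in tier 1 if hospitals enrol equally. Name that assumption and remove the implication that every tier reaches ±2.5%. This costs a few sentences in section 7 and the synopsis. It does mean that the factor of three needs a new justification.

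2. **Secure the split, if tier-level precision is wanted.** Set enrolment targets of about 1,644 per tier within the same total (3 × 1,644 = 4,932) and track them in the EDC system, or align the hospital mix with them.
   - With targets alone, at 62.5 patients per hospital in 6 months, tier 1 would need about 109.6 / 62.5 × 6 = 10.5 months to fill, against a 6-month enrolment period in a 24-month plan. Closing tiers at 1,644 while keeping to 6 months would give only about 1,644 + 1,563 + 938 = 4,145 enrolled.
   - With an aligned mix and equal enrolment per hospital, each tier needs about 80 / 3 = 27 hospitals. That is about 12 more in tier 1 and 13 fewer in tier 3, and the added sites must be qualified and approved.
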